### Study design

The study consists of a controlled trial (assessment) with hospital as cluster, with a pre- and a post-test assessment. In total 6 hospitals will participate, 3 hospitals in the intervention condition and 3 hospitals in the control condition. Hospitals are selected for the intervention condition based on the presence of a specialized palliative care team. In the hospitals in the control condition standard care (usual care) will be delivered to patients with COPD by their treating lung specialists. In the hospitals in the intervention condition all patients with COPD will receive standard care by their treating lung specialist and those patients that are indicated for proactive palliative care by our set of indicators will also be supported by a specialized palliative care team on a regular base. Baseline measurements of the intervention study will be assessed from all participating patients during hospitalization for AECOPD before start of the intervention. Follow-up measurements will take place every three months, starting from the moment of discharge for a period of one year or until death. The primary outcome measure of the indicator study is time to death for any cause. The primary outcome measure of the intervention study is the change in quality of life measured by the St George Respiratory Questionnaire (SGRQ) at three month after baseline. As pre-test assessment, data will be obtained from the databases of the participating hospitals over a one year period preceding the assessment. These data on hospital-level are necessary to be able to compare hospitals at baseline. As post-test assessment, retrospectively the medical files of all participating patients will be examined over the assessment period. The assessment will take 18 month; 6 month for inclusion and 12 months for follow-up. The post-test assessment will be performed in the 3 months after the assessment.

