#### Other study parameters

In order to take account of possible confounding variables, other parameters are: age, gender, marital status, socio-economic status, smoking history, condition of living (single, or living together), and place of living (home, residential home, or nursing home).

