### Randomization

Randomization will not take place. Hospitals will be selected for the intervention condition based on the presence of a specialized palliative care team in the hospital. In order to be able to compare the hospitals in the control- and the intervention condition a pre-test assessment will be performed.

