##### Lung specialist

The treating lung specialist will provide standard care (usual care) to the patients hospitalized for an AECOPD. After the patient has filled out and returned the questionnaires the lung specialist in the control- and the intervention condition will fill out a case report form (CRF). The CRF consists of questions about the measurement results of each indicator of the set of indicators. The set of indicators is represented in Table 1. Only in the intervention condition the lung specialist will check if a patient meets two or more criteria of the set of indicators for proactive palliative care.

**Table 1 T1:** Set of indicators for proactive palliative care

**A patient hospitalized for AECOPD is eligible for proactive palliative care when meeting two or more criteria of the following set of indicators:**	
1.	Hypoxaemia or hypercapnia at discharge
2.	Treatment of the exacerbation with Non Invasive Ventilation (NIV)
3.	Patient needs professional home care service for personal care after discharge
4.	Negative answer to the surprise question: ‘Would I (as lung specialist) be surprised if this patient would have a subsequent readmission for AECOPD within 8 weeks and/or would die in the next year?
5.	The diagnosis of a severe comorbidity such as:
	a. Non-curable malignity or
	b. Cor pulmonale (proven or non proven) or
	c. Proven Chronic Heart Failure (CHF) or
	d. Diabetes mellitus with neuropathy or
	e. Renal failure, clearance < 40 (GFR: in ml/min)
6.	CCQ total, day version ≥ 3
7.	MRC dyspnea = 5
8.	FEV1 (measured before AECOPD) < 30% of predicted
9.	BMI < 21 or unplanned weight loss (> 10% weight loss in last 6 months or > 5% in last month)
10.	Previous hospital admissions for AECOPD (last 2 years ≥ 2 and/or last year ≥ 1)
11.	Age > 70 years

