#### Post-test assessment

A post-test assessment will be performed in all participating hospitals. The medical files of all participating patients will be examined retrospectively regarding the assessment period on the following measures:

● Number and length of hospitalization of unexpected hospital admissions for AECOPD

● Number and length of hospitalization of unexpected ICU admissions for AECOPD

● Are the choices of Advance Care Planning (ACP) documented in the medical file? (when yes/when no)

● Place of death (ICU/hospital/hospice/nursing/home/at home)

● Is preferred place of death known? (when yes/when no)

● Has this wish come true? (when yes/when no)

● Length of survival after meeting conditions for proactive palliative care

● The primary and secondary measures of the indicator study

In order to take account of possible confounding variables, other parameters are: age, gender, marital status, type of admission, (acute or planned), condition of living (single, or living together), place of living (home, residential home, or nursing home), Gold stage, comorbidities, and date of diagnosis.

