#### Study parameter(s) intervention study

Frequencies, means and standard deviations will be used to describe the study variables. Differences between the study groups in baseline characteristics and clinical outcomes will be assessed and tested for statistical significance with the use of two-sided Fisher’s exact tests and chi-square tests for categorical variables and independent-samples t-tests for continuous variables. The primary study outcome measure of the intervention study is the change in the score on the SGRQ from baseline to 3 months: a paired *t*-test will be used to test the difference between the groups for statistical significance. Linear mixed models, with adjustment for baseline scores, will be used to study the effect of proactive palliative care on SGRQ outcomes during the follow-up period. The analysis follows the principle of intention to treat. Survival time will be calculated from the date of enrollment to the date of death with the use of the Kaplan-Meier method. A Cox proportional-hazard model will be used to assess the effect of proactive palliative care on survival, with adjustment for demographic characteristics.

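### Intervention hospitals are selected, not randomised, but the stated analyses adjust for no clinical severity, so case-mix differences can pass for, or hide, a treatment effect

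*Protocol article*

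**What the plan says.** All references are to the protocol article.

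- **Allocation.** The Randomization section states: "Randomization will not take place. Hospitals will be selected for the intervention condition based on the presence of a specialized palliative care team". Study design gives the size: "In total 6 hospitals will participate, 3 hospitals in the intervention condition and 3 hospitals in the control condition".
- **Confounders from questionnaires.** Other study parameters gives both the purpose and the list: "In order to take account of possible confounding variables, other parameters are: age, gender, marital status, socio-economic status, smoking history", followed by living condition and place of living.
- **Confounders from medical files.** Post-test assessment repeats that purpose and adds type of admission and "Gold stage, comorbidities, and date of diagnosis".
- **Severity indicators.** Under Lung specialist, a case report form with the result of each of the 11 indicators in Table 1 is completed in both conditions.
- **Analyses.** Study parameter(s) intervention study, under Statistical analysis, names a t-test (called paired) on the 3-month SGRQ change. Linear mixed models with baseline-score adjustment cover SGRQ during follow-up, and a Cox model for survival is fitted "with adjustment for demographic characteristics". Clinical outcomes are otherwise compared by Fisher's exact, chi-square and independent-samples t-tests.

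**The concern.** In a non-randomised comparison of six hospitals, the patients of the two arms may differ in how ill they are. The article foresees this and collects the data needed to deal with it. The analysis section then fixes adjustment sets that leave the clinical data out. GOLD stage, comorbidities, lung function, dyspnea grade and previous admissions appear in no stated treatment comparison. Age is the one indicator that the demographic adjustment of the Cox model would pick up.

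The Background itself links death after discharge mainly to the severity of the COPD and to particular comorbidities, and links readmission to functional limitation and poor quality of life. For survival and admissions, the omitted variables are therefore the ones that the article regards as prognostic. At stake are the primary SGRQ conclusion and the secondary conclusions on survival and admissions. Each could reflect who was admitted to which hospital as well as what the palliative care team did.

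**Working it through.** **Step 1: which collected variables reach which comparison.**

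| Comparison | Stated adjustment | Severity data used |
|---|---|---|
| SGRQ change at 3 months (primary) | none | none |
| SGRQ over follow-up, mixed model | baseline score | none beyond baseline SGRQ |
| Survival, Cox model | demographics | none beyond age |
| Admissions and other clinical outcomes | none | none |

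**Step 2: whether other features fill the gap.**
- The pre-test assessment holds hospital-level counts of admissions, patients, days and in-hospital deaths. It has no SGRQ and no patient severity, and it enters no stated model.
- Significance tests of baseline differences may show an imbalance but do not correct the estimate.
- A change score, or baseline SGRQ as a covariate, deals with differences in starting level. It does not deal with severity or comorbidity that affects the course over three months.
- The two-indicator threshold is a partial restriction. A patient who is over 70 with one admission in the last year qualifies, and so does a patient with many severe indicators.

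**Step 3: how much a case-mix shift could matter.** The article gives no case-mix difference, so the shift b in mean SGRQ change is an assumption.

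Inputs from Sample size calculation: 86 per arm, 10% loss, SD of change 16, ICC 0.01, three hospitals per arm. The 86 follows from the stated 64 per group:
- design effect 1 + (64/3 − 1) × 0.01 = 1.203
- 64 × 1.203 = 77.0
- 77.0 / 0.9 = 85.6, rounded up to 86

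The 64 does not follow from a difference of 9 and SD 16, which give 50 to 51. That is a separate matter without bearing here.

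Analysed per arm: 86 × 0.9 = 77.4.

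Standard error of the difference: 16 × √(2/77.4) = 2.572.

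Rejection limit: 1.96 × 2.572 = 5.041.

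With no treatment effect, P(reject) = 1 − Φ((5.041 − b)/2.572) + Φ((−5.041 − b)/2.572).

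| Assumed b | P(reject), confounding alone |
|---|---|
| 0 | 5% |
| 2 | 12% |
| 4 | 34% |
| 6 | 65% |

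The middle value of 4 is the score change that the article, under Patient questionnaires, treats as meaningful for a patient. It is a convenient anchor, not evidence about these hospitals.

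**Step 4: the opposite direction.** With the planned difference of 9 and no bias, the test rejects with probability 1 − Φ((5.041 − 9)/2.572) = 94%. If case mix works against the intervention by 4 points, the net difference is 5, and the probability falls to 1 − Φ((5.041 − 5)/2.572) = 49%.

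**Step 5: clustering kept apart.** If the test also ignores ICC 0.01, the design effect is 1 + (25.8 − 1) × 0.01 = 1.248 and the true standard error is 2.572 × √1.248 = 2.873. The rates for b = 0, 2, 4 and 6 become 8%, 15%, 36% and 63%. The 8% at b = 0 comes from clustering, not from confounding.

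**The case against.** The strongest defence has four parts.

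1. **Confounders are partly used.** A reader might infer that the collected confounders go unused. That is too strong. The demographic questionnaire covers nearly the list in Other study parameters, so demographic adjustment of the Cox model uses much of it. What is missing there is clinical severity.
2. **Some protection exists.** A reader might also infer that covariate adjustment is the only guard against confounding. It is not. The outcome is within-patient change, the mixed models carry the baseline score, and the sample size counts only patients with a poor prognosis by indicators recorded in both arms. These measures stand as partial protection.
3. **The size is assumed.** Nothing in the article shows that case mix shifts an arm's mean change by 4 points, and the direction is unknown. That is why a range is shown. Setting 36% against a nominal 5% would also mix in the clustering defect. The confounding part at 4 points is 34%.
4. **A condensed article may leave covariate lists to a fuller plan.** This would carry weight if the article were silent. It names the primary test and the adjustment sets, and following it as written gives an estimate unadjusted for severity.

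It is also tempting to argue that excluding patients already under a palliative care team removes more patients from the intervention hospitals. The Discussion says that patients with COPD have so far hardly received palliative care, which suggests few such exclusions in either arm. That argument is not relied on here.

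**Conclusion.** The point holds for clinical severity. The stated primary comparison has no covariates, and no stated treatment comparison uses GOLD stage, comorbidities or the clinical indicators, against the article's own purpose in collecting them. Case-mix differences can be read as a treatment effect or can hide one. The documents do not support saying that they will be, or in which direction.

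Under the assumptions shown (77 analysed per arm, SD 16, independent patients, an assumed shift of 2 to 6 points), confounding alone takes the false-positive rate from 5% to between 12% and 65%. The survival outcome is secondary, so the weight of the point lies mainly on the primary SGRQ comparison.

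Adjustment would reduce the problem but not solve it. With three selected hospitals per arm, hospital-level differences cannot be separated from the intervention. The paired label on the t-test and its neglect of clustering are separate defects.

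**What to change.** - Make the primary 3-month SGRQ comparison a regression or mixed model with a short prespecified covariate list: baseline SGRQ, age, sex, GOLD stage or FEV1 % predicted, MRC dyspnea, previous AECOPD admissions, severe comorbidity and living situation. A propensity score on these variables is an alternative that saves degrees of freedom.
- Add the same severity variables to the Cox model and to the admission comparisons.
- Use values as they stood at inclusion, since GOLD stage and comorbidities come from a retrospective file review.
- Report the unadjusted comparison as secondary.
- State in the analysis section and in the conclusions that hospital-level confounding cannot be removed with three selected hospitals per arm.

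All variables are already collected through the case report form, the patient questionnaires or the medical files, so no new data collection is needed. The cost is revised analysis wording, a rule for missing covariates and a few degrees of freedom out of about 154 analysed patients (2 × 77).

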### Ethical considerations

Patients with COPD who participate in the study may be vulnerable but are certainly capacitated adults. Since this is a therapeutic research the participants, patients and informal caregivers, may even benefit from participation. The potential risks of this study are quite small. They relate to the burden of filling in questionnaires. This will take the patient about 20–30 minutes every three months. The potential benefits on the other hand are comparatively large. First, participating patients with severe COPD and their informal caregivers in the intervention condition will get, if indicated for it, extra proactive palliative care. Second, this study may lead to better understanding of the conditions to start and the effectiveness of proactive palliative care for patients with COPD. Third, there is a potentially benefit for society since results of this study may ultimately lead to different and improved clinical approaches to care of patients with severe COPD.

This Study has been approved by the Medical Ethics Committee (CMO) of the Radboud University Nijmegen Medical Centre (METC protocol number 2012/260).

## Discussion

Research on the effectiveness of palliative care for the COPD patient is scarce and inconclusive [52]. The PROLONG study is the first prospective controlled trial evaluating the effectiveness of a multidisciplinary approach to palliative care in COPD disease. The outcomes of this study will give insight in the discriminating power of a set of indicators for proactive palliative care and the effectiveness of proactive palliative care for patients with COPD.

In the Netherlands, COPD is on the sixth place of causes of death for people older than 45 years. In 2011 6,535 patients died with COPD as primary cause of death while in 2010 the number of hospitalizations of patients with COPD as diagnosis was 22,5440. The prevalence of COPD in the Netherlands is high (361,800 in 2011) and will, with the aging of the population, further increase the coming years [53]. Up to now patients with COPD hardly receive palliative care. The above mentioned numbers reveal the social relevance of introducing palliative care for patients with COPD. Furthermore, introducing palliative care for patients with COPD can possibly be cost-saving since palliative care may lead to reduction of acute care [33,54,55].

We have chosen a cluster controlled design for the PROLONG study to prevent cross-contamination of the intervention within a hospital. At the moment of recruitment of hospitals the minority of hospitals in the Netherlands had the availability of a specialized palliative care team. Therefore, it was not an option to perform a randomized cluster controlled trial. Hospitals are selected for the intervention condition based on the presence of a specialized palliative care team in the hospital. In order to be able to compare the hospitals in the control- and the intervention condition at baseline a pre-test assessment will be performed.

Recruitment for trials of patients with poor prognosis is often difficult. In order to ensure a sufficiently large sample for the PROLONG study broad inclusion criteria will be used. All patients hospitalized with an AECOPD over 17 years old can be screened for the study. This will facilitate lung specialists to include patients. Only after inclusion the distinction between patients with poor or better prognosis will be made in order to decide who is eligible for the intervention condition.

The PROLONG study may lead to better understanding of the conditions to start and the effectiveness of proactive palliative care for patients with COPD. The innovative aspects of the PROLONG study are: 1) the use of a set of indicators to identify patients hospitalized with an AECOPD who are in need of proactive palliative care, 2) the active involvement of a specialized palliative care team in the development and the implementation of proactive palliative care for patients with COPD and, 3) the use of a patient-tailored proactive palliative care plan in which lung specialist and a specialized palliative care team work together to optimize proactive palliative care for the COPD patient. This patient-tailored proactive palliative care plan is intended to meet and to adjust to the individual needs, wishes, possibilities and limitations of the patient and the informal caregiver.

## Abbreviations

ACP: Advance care planning; AECOPD: Acute exacerbation chronic obstructive pulmonary disease; BMI: Body mass index; CCQ: Clinical COPD questionnaire; CHF: Chronic heart failure; COPD: Chronic obstructive pulmonary disease; CRF: Case report form; FEV1: Forced expiratory volume in 1 second; GP: General practitioner; GRF: Glomerular filtration rate; HADS: Hospital Anxiety and Depression Scale; ICU: Intensive care unit; IQR: Inter quartile range; MRC dyspnea: Medical Research Council dyspnea questionnaire; MUST: Malnutrition Universal Screening Tool; NIV: Non-invasive ventilation; PNPC-sv: Problems and needs in palliative care questionnaire short version; PPCPC: Proactive palliative care planning card; QOL: Quality of life; RCT: Randomized controlled trial; SD: Standard deviation; SGRQ: St George Respiratory Questionnaire; SPPIC: Self-perceived pressure from informal care questionnaire; WHO: World Health Organization.
